##### Recruitment

We will recruit up to 740 people who use crack through participating specialist drug services at the intervention (*n* = 400) and control sites (*n* = 200) and via peer networks (*n* = 140). Peer network recruitment will happen at both intervention (*n* = 100) and control sites (*n* = 40).

We will recruit using both randomised and targeted sampling. We will attempt to recruit a randomised sample from specialist drug services, to reduce selection bias, but will be pragmatic considering difficulties in recruiting this marginalised population. The LSHTM team will work with specialist drug services to generate a randomised anonymised sample of clients who are eligible to participate in the study. The specialist drug services will start recruitment from this list contacting potential clients in line with standard service engagement practice and where appropriate invite people in to participate in the research. Should we fail to meet recruitment targets at week eight, recruitment will be opened to all eligible clients, irrespective of the list, including those attending for appointments, opportunistic walk-ins and referrals from friends. In addition, we will employ targeted sampling methods to recruit 140 participants representing diverse crack user sub-populations via peer networks to widen the evidence base on health needs and service access among people who use crack not currently engaging with services. Both pre- and post-surveys recruitment will be conducted over the course of 10 weeks with an additional 4-week extension if necessary.

##### Sample size

A sample of 306 (204 SIPP, 102 control) is sufficient to compare proportional differences in pipe sharing at 90% power with significance of *p* = 0.05. We assume 52% will share pipes, and that there will be a difference of 20% (52% to 32%) between control and intervention; substantiating previous evidence suggesting pipe provision reduces prevalence of sharing from 37 to 12% over a 6 month period [16]. An inflated sample of 740 (500 SIPP, 240 control) allows for linkage of 75% of participants between baseline and follow-up surveys and for multivariable analyses to adjust for any baseline differences in characteristics between intervention and control sites (see Fig. 3).

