##### Data collection

Two surveys will be conducted six months apart to allow for the intervention phase. For both the pre- and post-survey, a structured questionnaire will be administered by staff at specialist drug services and peer researchers, trained in data collection methods, informed consent procedures and all aspects of the study protocol. Service providers and peers will approach potential participants and current clients, describe the study and discuss contents of the information sheet and consent form. Participants who consent will complete a structured questionnaire in English on a Lenovo tablet device with the ODK collect app either self-completed or administered by a service provider or peer. The questionnaire takes approximately 30 min to complete and contains the follow sections: demographics (including age, gender identity, sexual orientation, ethnicity, and source(s) of income); drug use practices (including drugs taken, routes of administration, and equipment sharing/reuse); indicators of social exclusion (including housing status and healthcare access); policing (including recent arrest and history of incarceration); primary and secondary outcomes (see below). Our questionnaire has been developed with input from peers and service providers and incorporates measures used in comparable surveys with people who use crack in Canada and UK [2, 18, 27, 28, 30, 42] as well as drawing on a questionnaire piloted by peers in 2020 for SIPP study conceptualisation. We will not actively follow-up participants, but we will collect minimal identifiers (date of birth, initials) needed to link people over time to allow assessment of primary and secondary outcomes and new presentations at specialist drug services. The same questionnaire will be used to collect post-intervention survey data.

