Appropriate statistical models will be selected based on evidence of clustering observed. The model will include fixed effects for time and treatment, and we will explore the appropriateness of including a random effect to account for heterogeneity of participants within sites or a fixed effect to account for heterogeneity across sites. We will explore the need to adjust for clustering within treatment site and by sites using intra-class correlation coefficients. Fourthly, we will examine evidence of a dose–response relationship between intensity of exposure to SIPP and primary and secondary outcomes using logistic regression models and categorising exposure to SIPP as a continuous or categorical variable (1, 2–3, 4–5,6 + exposures) depending on the distribution of contacts with SIPP in the intervention sites.

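### The 90% power stated for 306 belongs to an unclustered, single-survey comparison. The planned change comparison across six sites has no stated power, and the 75% linkage behind 740 is unsupported.

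*Protocol article*

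**What the plan says.** All references are to the protocol article, under Impact evaluation unless noted.

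- **Sample size.** "A sample of 306 (204 SIPP, 102 control) is sufficient to compare proportional differences in pipe sharing at 90% power". The inputs are: "We assume 52% will share pipes, and that there will be a difference of 20% (52% to 32%) between control and intervention". The total is then raised to 740 (500 SIPP, 240 control), which "allows for linkage of 75% of participants between baseline and follow-up surveys and for multivariable analyses to adjust for any baseline differences". No ICC, design effect, within-person correlation or variance for a difference in change is given.
- **Abstract and Recruitment.** About 740 is the target at each survey point: 400 + 100 at intervention sites and 200 + 40 at control sites.
- **Analysis.** The primary estimate is the change in pipe sharing at intervention sites compared with control sites. It uses every participant, whether or not that person appears in both surveys. The model has fixed effects for time and treatment. On sites: "We will explore the need to adjust for clustering within treatment site and by sites using intra-class correlation coefficients".
- **Study partners and sites, Table 2.** SIPP is supplied in three areas (Bristol, Nottingham, Mansfield) and compared with three (Birmingham, Coventry, Warwickshire).
- **Data collection.** "We will not actively follow-up participants"; people are linked afterwards by date of birth and initials.

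**The concern.** The power statement and the planned analysis concern different quantities. A single comparison of two proportions carries the sampling error of one survey. A difference between two changes carries the error of both surveys. Because SIPP is allocated by area, site-to-site variation in how sharing moves over time also enters the error. None of this is in the calculation, and the reasons given for 740 do not cover it.

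The study is meant to inform a review of legislation. If it finds no clear difference, readers will set that result against the stated 90%. They need to know that this figure is not the power of the planned comparison.

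Separately, the linked analyses depend on 75% of people reappearing in the second survey, for which the article gives no mechanism or data.

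**Working it through.** **Inputs from the article:** 52% and 32%; significance level 0.05 (taken as two-sided, which reproduces the figure); 90% power; 204/102 and 500/240; three sites per group. **Assumed:** 52% sharing in both groups before the intervention; the ICC; the between-wave site correlation c; the within-person correlation.

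**1. The plan's own figure.** With ratio r = 2, pooled p = (0.52 + 2 × 0.32)/3 = 0.3867.

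n(control) = [1.960 × √(1.5 × 0.3867 × 0.6133) + 1.2816 × √(0.2496 + 0.2176/2)]² / 0.20² = 93.7.

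Continuity correction: (n/4) × [1 + √(1 + 2(r+1)/(n × r × 0.20))]² = 101.1, rounded up to 102. SIPP is 2 × 102 = 204 and the total is 306, exactly as stated. Without the correction it is 94 + 188 = 282. So 306 assumes independent people at one time point.

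**2. The change contrast, no clustering, unlinked surveys.**

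Variance = 2 × 0.2496/nC + (0.2496 + 0.2176)/nI; power = Φ(0.20/SE − 1.960).

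- 102/204: 0.004894 + 0.002290 = 0.007184; SE 0.0848; 0.20/SE = 2.36; power about 66%.
- 240/500: 0.002080 + 0.000934 = 0.003014; SE 0.0549; 0.20/SE = 3.64; power about 95%.
- For 90% at 2:1: nC = (1.960 + 1.2816)² × (0.4992 + 0.4672/2)/0.04 = 10.507 × 0.7328/0.04 = 192.5, so 193 + 385 = 578 per survey.

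With 75% linkage and an assumed within-person correlation of 0.3 to 0.5, each group's variance falls by 2 × 0.75 × ρ × √(v0·v1)/n. Power is then 76% to 85% at 306 and 98.5% to 99.6% at 740.

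**3. Site clustering at 740.** Site sizes are m = 240/3 = 80 and 500/3 = 166.7 per survey. With v0 and v1 the pre and post variances, each group contributes

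[(v0 + v1) × ((1 − ICC)/m + ICC) − 2 × √(v0·v1) × ICC × c] / 3.

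Example, ICC 0.02 and c = 0.5: 0.003702 (control) + 0.002477 (SIPP) = 0.006179; SE 0.0786; power 72%.

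| Comparison at 740 (normal theory) | ICC 0.01 | ICC 0.02 | ICC 0.05 |
|---|---|---|---|
| Change, c = 0 | 72% | 54% | 31% |
| Change, c = 0.5 | 84% | 72% | 48% |
| Change, c = 0.8 | 91% | 87% | 73% |
| Post-survey only | 95% | 84% | 55% |

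The last row uses variance 0.2496 × (1 + 79 × ICC)/240 + 0.2176 × (1 + 165.7 × ICC)/500. Solving the change formula for 90% power gives a tolerable ICC of about 0.0025, 0.005 and 0.013 at c = 0, 0.5 and 0.8.

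**4. Linkage.** 0.75 × 740 = 555 linked people. The linked set would fall to 306 at 306/740 = 41% linkage. The article gives neither the size of the eligible client pool nor whether the second survey reuses the first client list, so the expected linkage cannot be computed.

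**The case against.** The strongest reply is that nobody plans to recruit 306. The study plans 740 per survey, more than the 578 that the change contrast needs before clustering, and power there is about 95%. That stands. A reader might infer that 740 is too small, or that the study could easily miss a 20-point effect. The document does not support either, because any shortfall depends on an ICC and a between-wave site correlation that it does not give. If site differences are stable between surveys (c = 1), the formula in step 3 returns about 95% to 96% across the same ICC range.

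It can also be said that the effect measure is not unambiguous. The Analysis section speaks of a change, but also of logistic regression comparing groups after the intervention, adjusted for primary outcome measures, and it names no interaction term. On a post-survey reading, 740 gives over 99% unclustered and 95% at ICC 0.01. This stands in part: clustering still matters on that reading (84% and 55% at ICC 0.02 and 0.05).

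Next, 306/0.75 = 408, so 740 leaves a margin of 740/408 = 1.81, and the Analysis section does plan to look at clustering. Both are true. But the article assigns that margin to covariate adjustment. For a single-survey comparison of the 555 linked people (92.5 per site), it would absorb an ICC of only (1.81 − 1)/91.5, or about 0.009.

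Few-cluster inference should not be overplayed. A site-level t test on 4 degrees of freedom would give only 78% at 740 even with ICC 0, but the plan specifies an individual-level analysis and states no such test.

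Finally, a reader might infer that the design cannot yield 75% linkage. That goes beyond the text. Without the pool size or the second sampling list, unsupported is as far as the document allows.

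**Conclusion.** The point holds as a mismatch between the stated power and the planned analysis. The 90% for 306 is correct for independent people in one post-survey comparison. For the change contrast it is about 66%, given 52% sharing in both groups beforehand and unlinked surveys, and this part needs no ICC.

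At 740 the position is open. Power is about 95% without clustering and anywhere from 31% to 91% over the assumed ICC range of 0.01 to 0.05 and between-wave site correlation of 0 to 0.8. The sample-size text makes no allowance for clustering, so it does not show that 740 keeps 90%; nor does it show the reverse.

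The claim that 740 "allows for linkage of 75% of participants between baseline and follow-up surveys" has no stated basis. Its reach is limited: the primary analysis uses everyone, linked or not, and only the sensitivity and per-protocol analyses depend on the linked set.

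This should be fixed, because the stated power will frame how the result is read. It does not invalidate the design.

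**What to change.** Restate the Sample size paragraph:

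1. Label 306 as the size for a single-time-point comparison of independent people, with no allowance for clustering.
2. State power at 740 per survey for the group-by-wave effect, over a range of ICC and between-wave site correlation with six sites, and note that inference suited to so few sites would lower it further.
3. Either justify the 75% linkage, or describe the surveys as repeated cross-sections with an exploratory linked subset of unknown size.

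No participants are added and the design does not change. The cost is a stated power that is less favourable and given as a range.

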**Fig. 3 Fig3:**
[figure not shown]
Impact evaluation sampling strategy

##### Analysis

We will analyse quantitative data in four ways. Firstly, we will describe demographic characteristics, drug use behaviours, and indicators of social exclusion among PWUC stratified by exposure group at the pre- and post-survey time points. Secondly, we will estimate the change in primary outcome (sharing of pipes in past 28 days) for participants in intervention sites compared to control sites. Logistic regression will be used to compare baseline prevalence of primary and secondary outcome measures between intervention and control sites post-intervention. Primary analysis will use an adjusted, individual-level intention-to-treat approach, including all participant data (irrespective of baseline and follow-up participation, their engagement with SIPP and assuming missing observations are missing at random) in order to reflect the effects of SIPP in every day practice. The same analysis plan will be used for secondary outcomes (use of homemade pipes, cuts/burns, injecting, and service engagement). Linear regression models will compare baseline frequency of injecting between intervention and control sites and estimate relative changes in mean frequency of injecting. Logistic and linear models will adjust for a priori confounders including sex, age, duration of crack use, engagement in services, primary outcome measures, and any variables with evidence of imbalance described above. As a sensitivity analysis will focus on participants for which we have baseline and follow-up (though data linkage) to assess changes in outcomes over time and between intervention and control. Thirdly, we will undertake a per-protocol analysis, limiting the analyses to participants with both baseline and follow-up data and who report use of SIPP. This will give a measure of efficacy where SIPP is delivered in the optimal way.

Appropriate statistical models will be selected based on evidence of clustering observed. The model will include fixed effects for time and treatment, and we will explore the appropriateness of including a random effect to account for heterogeneity of participants within sites or a fixed effect to account for heterogeneity across sites. We will explore the need to adjust for clustering within treatment site and by sites using intra-class correlation coefficients. Fourthly, we will examine evidence of a dose–response relationship between intensity of exposure to SIPP and primary and secondary outcomes using logistic regression models and categorising exposure to SIPP as a continuous or categorical variable (1, 2–3, 4–5,6 + exposures) depending on the distribution of contacts with SIPP in the intervention sites.

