In this paper, we introduce the National Institute for Health and Care Research (NIHR)-funded SIPP (Safe inhalation pipe provision) study, which commenced in July 2022 and will run until February 2025. We provide the study protocol and discuss implications for impact. To our knowledge, this study is the first of its kind globally and has been designed to meet a pressing need in the UK context, given increasing use of crack cocaine and the high prevalence of COPD among people who smoke crack and/or heroin [23, 34–36]. Alert to the heightened risk of pipe sharing and unsafe equipment use for people with respiratory vulnerabilities, members of the study team advocated for a relaxation of restrictions to allow for crack pipe provision during the COVID-19 pandemic. This application, for a government supported memorandum of understanding between police and providers, was unsuccessful due to concerns about promotion of crack use and a dearth of UK evidence [12]. The SIPP study was designed to address these concerns, with a methodologically rigorous pre- and post-intervention survey component with non-equivalent control sites, complemented by a process evaluation and peer research capacity building in geographically diverse sites, as outlined below. Our study is designed to answer the question: “To what extent and how does SIPP reduce health risks and enhance service engagement among people who use crack cocaine?”.

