##### Outcome measures

Our primary outcome measure is a decrease in the proportion of participants self-reporting sharing of crack pipes in the past 28 days (yes/no).

Secondary outcomes comprise:increased presentations at specialist drug services defined as: a) the change in proportion of attendances at specialist drug service sites in the past 6 months (number of new attenders in past 6 months/total number of clients) measured through data linkage to drug service records; and b) the change in proportion of participants attending a specialist drug service in the past 6 months (measured through self-report yes/no)reduction in injecting frequency defined as number of times injected in the past 28 daysreduction in number of days sharing pipes in the past 28 daysdecrease in proportion of those reporting current acute injuries defined as cuts/burns to mouth or lips in the past 28 days (yes/no)reduction in the proportion of participants who use homemade pipes in the past 28 days (yes/no)reduction in proportion of participants using ash as a crack suspension device in the past 28 days (yes/no)reduction in proportion of participants reporting respiratory risk markers defined as difficulty breathing, chest pain, coughing blood in the past 28 days (yes/no).

Our primary and most of our secondary outcomes are self-reported. Self-report measures of drug-related risk behaviours are deemed reliable, particularly when used with computer assisted survey instruments [43, 44]. The use of self-reported measures in evaluating the impact of harm reduction interventions such as NSPs is widespread [45]. Self-reported crack pipe sharing has been used as an outcome measure for Canadian studies [18, 27, 46] aiding comparability. Service presentations will be assessed through the collection of minimum identifiers (initial and date of birth) for participants in pre- and post-surveys and from each person obtaining a SIPP kit as part intervention monitoring for the process evaluation (see below). These minimum identifiers will be used to link data from surveys and SIPP monitoring, and also allow linkage of both survey and SIPP monitoring data with specialist drug services client lists before and after the intervention to review increased service presentation due to SIPP.

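### The primary model adjusts for service engagement and for the primary outcome without saying when they are measured; same-survey values condition on outcomes, and baseline values are missing for about a quarter of the stated sample

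*Protocol article*

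**What the plan says.** All references are to the Protocol article.

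- **Covariates** (Impact evaluation, Analysis): "Logistic and linear models will adjust for a priori confounders including sex, age, duration of crack use, engagement in services, primary outcome measures", together with "any variables with evidence of imbalance described above". No time of measurement is given for engagement or for the primary outcome. The description that the second phrase points back to covers demographics, drug use behaviours and social exclusion at both survey points.
- **Primary sample** (same section): the intention-to-treat analysis is described as "including all participant data (irrespective of baseline and follow-up participation, their engagement with SIPP and assuming missing observations are missing at random". The comparison restricted to linked participants is placed as a sensitivity analysis.
- **Secondary outcomes** (same section): "The same analysis plan will be used for secondary outcomes (use of homemade pipes, cuts/burns, injecting, and service engagement". So the covariate list also applies when service engagement is the response.
- **Engagement as an outcome**: the first secondary outcome is "increased presentations at specialist drug services defined as" two measures, one of them "the change in proportion of participants attending a specialist drug service in the past 6 months (measured through self-report yes/no". The study question in Background is "To what extent and how does SIPP reduce health risks and enhance service engagement among people who use crack cocaine".
- **Design**: Data collection says there is no active follow-up and that people are linked across surveys by date of birth and initials. Sample size plans for 75% linkage and gives baseline differences between sites as a reason for adjusting. Analysis names fixed effects for time and treatment; an interaction between them is not explicitly stated.

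**The concern.** In a non-randomised comparison, covariate adjustment carries much of the causal claim, so the covariates need to be fixed before the intervention and available for the people analysed. Two of the listed covariates are outcomes of the study. Depending on when they are taken, they are either affected by SIPP (or identical to the response), or absent for anyone who cannot be linked to a pre-survey record. Two analysts could follow the sentence faithfully and estimate different effects in different populations. The study is meant to inform a review of legislation, so this choice should not be left open.

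**Working it through.** **1. The sample size is not at fault.** Inputs from Sample size: 52% against 32%, 90% power, alpha 0.05 (taken as two-sided), allocation 2:1.

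- Pooled proportion = (0.52 + 2 × 0.32)/3 = 0.3867.
- n(control) = [1.960 × √(0.3867 × 0.6133 × 1.5) + 1.282 × √(0.52 × 0.48 + 0.32 × 0.68/2)]² / 0.20² = 93.7.
- Continuity correction: (93.7/4) × [1 + √(1 + 2 × 3/(93.7 × 2 × 0.20))]² = 101.1, rounded up to 102.
- Total = 102 + 204 = 306, the protocol's figure.

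**2. Reading A: values from the same survey.**

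- For the primary outcome, sharing in the past 28 days would be both response and covariate. That is not a usable model. The same holds for engagement when engagement is the response.
- For the sharing model, engagement at the post-survey is a post-intervention variable. Its recall window is six months (about 26 weeks). The post-survey runs for 10 weeks after the intervention, or 14 with the extension. Even the latest respondent's window therefore contains about 26 − 14 = 12 weeks of the intervention.

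Illustration, with inputs that are assumptions and not in the protocol: 50% of controls are engaged, SIPP raises this by 10 to 30 points, and engagement has an odds ratio of 0.7 to 0.3 with sharing. Marginal sharing is held at 52% and 32%, so the total effect is −20.0 points (odds ratio 0.434). The adjusted difference is standardised to the pooled 2:1 engagement distribution:

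adjusted difference = (1 − e) × (difference among the non-engaged) + e × (difference among the engaged).

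| SIPP effect on engagement | OR, engagement with sharing | e | Non-engaged, SIPP − control | Engaged, SIPP − control | Adjusted difference | Conditional OR |
|---|---|---|---|---|---|---|
| +10 points | 0.7 | 0.567 | 36.7 − 56.4 | 28.9 − 47.6 | −19.1 points | 0.447 |
| +30 points | 0.3 | 0.700 | 54.4 − 66.6 | 26.4 − 37.4 | −11.4 points | 0.600 |

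Check of the last row: 0.30 × (−12.2) + 0.70 × (−11.0) = −11.4. If SIPP does not change engagement, or engagement is unrelated to sharing, the risk difference stays at −20.0.

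**3. Reading B: pre-survey values.** Assume the post-survey also reaches 740.

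- Linked: 0.75 × 740 = 555 (375 SIPP, 180 control).
- Without a baseline value: 740 − 555 = 185, or 25%.
- Power for 52% against 32% (normal approximation, no continuity correction, no clustering): 99.9% with 740 and 99.5% with 555.

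So the cost is a changed population, not lost power: a complete-case fit is carried out on the people reserved for the sensitivity analysis. If both waves are pooled, as the time effect suggests, pre-survey sharing is also the response in the pre-survey rows. Using it as a covariate there is circular even for linked people.

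**4. The readings can mix.** The only engagement report from an unlinked post-survey participant is the post-survey one. Filling the baseline gap with it brings back Reading A for that quarter of the sample.

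**5. Data-driven covariates.** The imbalance clause points to a description of both waves. A post-survey difference in a drug use behaviour that SIPP itself produced could therefore qualify as a confounder.

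**The case against.** The strongest defence is that the protocol means baseline values. It calls these variables confounders, and Sample size gives baseline differences as the reason for adjusting. On that reading nothing of the effect is removed, and the missing-at-random assumption leaves room to impute values for unlinked people. A site-level baseline prevalence could also serve without any individual linkage. Covariate timing and the imputation method are details that an article may leave to a fuller plan.

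Much of this stands, and it rules out several stronger statements that a reader might infer:

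- **That the adjusted estimate necessarily loses part of the effect.** This needs post-intervention values. The visible text sets engagement beside risk reduction as a joint aim; it does not say that SIPP reduces sharing through engagement, and the logic model figure is not shown. Services also hand out the kits, so even the direction of bias is open.
- **That the model cannot be fitted.** Imputation is possible under the stated assumption.
- **That most participants lack a baseline value.** The protocol plans for 75% linkage. Whether that is achievable is a separate question.

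What does not stand is that this is only missing detail. The article names the covariates, names the sample and applies the plan to engagement as an outcome, and these statements do not fit together without a correction. A site-level baseline value is nowhere described, and it would be absorbed by the site fixed effect that the protocol is considering.

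**Conclusion.** The point holds in a conditional form. As written, the adjustment list contains a secondary outcome that SIPP targets and the primary outcome itself, gives no time point for either, and conflicts with an analysis of all participants.

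- **Same-survey values:** the model conditions on the response and on a post-intervention variable. The size and direction of the bias are not determined by the documents. The range of −19.1 to −11.4 points against a true −20.0 is an illustration under assumed inputs, not an estimate.
- **Baseline values:** no effect is adjusted away, but 185 of 740 post-survey participants (25%, assuming the planned 75% linkage and a full second survey) have none. Without imputation, the primary analysis becomes one of the 555 linked people.
- **Imbalance clause:** it could admit covariates changed by SIPP; the text does not show that it would.

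The baseline reading is the more natural one, but each reading needs the text to be amended.

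**What to change.** Rewrite the covariate sentence of the Analysis section along these lines:

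1. In the all-participant model, treat pre-survey sharing as a response. State a group-by-wave interaction explicitly as the effect of interest, and remove primary outcome measures from the covariates. The removal depends on that interaction being written in.
2. Adjust for site, sex, age, duration of crack use and recruitment source (specialist service or peer network, which the recruitment targets fix).
3. Do not adjust for engagement reported at the post-survey. In practice engagement leaves this model unless pre-survey values are imputed for unlinked people.
4. State that no outcome appears in its own covariate list in the all-participant model.
5. Choose any additional covariates from pre-survey imbalance only.
6. Use a person's own pre-survey sharing and engagement in the linked sensitivity analysis, or in the full sample with multiple imputation under the stated missing-at-random assumption.

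The cost is a change of text and one explicit model term; no new data or larger sample is needed. There is a small loss: less control for changes in the engagement mix within a site between waves, for example if recruitment opens to walk-ins and referrals at week eight in one survey and not the other. Site and recruitment source do not fully cover that. The linked or imputed analysis in item 6 is the check on it.
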